#### Primary feasibility outcomes

Recruitment and retention rates: the study will monitor the number of participants enrolled and retained throughout the trial to assess whether the target sample size can be achieved within the planned timeframe.Fidelity of IPS implementation: adherence to core IPS principles will be measured using the IPS Fidelity Scale.Acceptability and perceived barriers: qualitative interviews and focus groups with stakeholders (e.g., participants, providers, employers) will explore the acceptability of the IPS model and perceived barriers to its implementation.

#### Secondary participant-centered outcomes

These outcomes will capture individual-level changes related to employment, financial stability, and health. A detailed schedule of assessments is presented in Table 3.Employment outcomes: monthly employment status (employed/not employed), job start and end dates, average hours worked per week, and hourly wages.Financial well-being: annual income, income sources, and housing stability over the past 12 months.Health-related outcomes: use of health services (e.g., hospitalizations, emergency visits) and self-reported measures of general health and functioning.

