### Aims and objectives

The primary aim of this pilot randomized controlled trial is to evaluate the feasibility and contextual fit of an adapted version of the Individual Placement and Support (IPS) model for people with serious mental illness (SMI) within the Jalisco mental health system in Mexico. The specific objectives are:To adapt the IPS model to the Jalisco context, based on input from stakeholders including policymakers, service providers, users, and employers. This process will identify contextual barriers and inform modifications to IPS materials, delivery format, and fidelity criteria. The adapted model will be implemented through blended training (virtual and in-person sessions, e-learning resources).To assess the feasibility of implementing the adapted IPS model, including recruitment and retention rates, acceptability among stakeholders, and fidelity of delivery. Qualitative data will be collected to explore perceived facilitators and barriers to implementation.To explore preliminary outcomes related to employment, financial well-being, and health among participants. Outcomes will be compared between intervention and control groups at baseline, 6 months, and 12 months.To evaluate implementation processes and resource needs, including patterns of participation and fidelity over time, multilevel barriers and facilitators (e.g., at the provider and system level), and resource requirements (e.g., personnel, time, and infrastructure) for potential scale-up.

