#### Outcomes

This study will assess feasibility outcomes related to the implementation of the IPS model and explore its preliminary effects on participant employment, financial well-being, and health-related outcomes. The evaluation will emphasize feasibility outcomes, while participant-centered outcomes will provide additional insight into the model’s potential impact. Data will be collected at baseline and through quarterly follow-up interviews. All instruments will be administered in Spanish; if no validated Spanish version exists, the measure will be translated using forward–back translation by bilingual specialists, followed by expert panel review to ensure conceptual equivalence and linguistic clarity. Table 3 provides a detailed summary of all planned outcomes and associated measures.

**Table 3 Tab3:** Outcomes and measures

Measure	Data Source	Interval (duration)	Constructs Addressed
Baseline participant interview	Participant	Baseline (45–60 min)	- Demographics (age, sex, gender, marriage status, race/ethnicity)—employment history (past year and past 5 years)—income history (annual income, income sources)—Housing history (past 5 years)—health service utilization history (past-year hospitalization and emergency service utilization, regular medical care)—health and functionality (Brief Psychiatric Rating Scale (BPRS), Medical Outcomes Study Short-Form 12-Item (SF-12, mental and physical), Social Occupational Functioning Scale (SOFS), Recovery Assessment Scale (RAS-24)—Social capital (numbers, education, and justice system involvement of parents, siblings, children, and friends)—Justice system involvement (arrest, incarceration, and conviction history)
Quarterly employment interview	Participant	Quarterly (10 min)	- Past-quarter employment (any competitive employment; per-job weeks worked, hours worked per week, hourly wage, job start/end dates if applicable)
Follow-up participant interview	Participant	6, 12 months (40–50 min)	- Housing (past 6 months)—health service utilization (past 6 months hospitalization and emergency service utilization)—health and functionality (Brief Psychiatric Rating Scale (BPRS), Medical Outcomes Study Short-Form 12-Item (SF-12, mental and physical), Social Occupational Functioning Scale (SOFS), Recovery Assessment Scale (RAS-24)

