#### Participant timeline

The schedule of enrollment, intervention delivery, and outcome assessments is summarized in Table 5. Participants will be followed for 12 months, with assessments conducted at baseline and quarterly thereafter.

**Table 5 Tab5:** Participant timeline

Study period	Enrollment	Allocation	Post-allocation	Close-out
Timepoint (quarterly)	-q1	0	q1	q2
Enrollment:				
Eligibility screen	X			
Informed consent	X			
Allocation		X		
Interventions:				
IPS services			X	
Usual services			X	
Assessments:				
Baseline variables	X	X		
Quarterly employment interview			X	X
Follow-up participant interview			X	
IPS Participation Measure (monthly)			X	X
IPS Employment Specialist Log (monthly)			X	X

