### Data collection and management

#### Plans for assessment and collection of outcomes

Baseline structured interviews will be conducted prior to randomization to collect data on demographic characteristics, social capital, physical and mental health status, health service utilization, justice system involvement, functionality, and employment and financial history [21]. Validated instruments with established psychometric properties and Spanish versions will be used at baseline and follow-up assessments. These include the Brief Psychiatric Rating Scale (BPRS) for psychiatric symptoms [22], the Medical Outcomes Study Short-Form 12-Item (SF-12) for physical and mental health [23], the Social and Occupational Functioning Scale (SOFS) for functioning and role performance [24], and the Recovery Assessment Scale (RAS-24) to assess perceived recovery and empowerment [25]. All instruments will be administered by trained research staff using structured protocols to ensure consistency and data quality.

Quarterly structured follow-up interviews will assess employment status during the prior 3 months. Data collected will include job titles, employment dates, hours worked, and wages earned. When applicable, the reason and timing of job termination will also be recorded [21]. These structured interviews will be conducted in person at the Center for Comprehensive Care in Long-Stay Mental Health, subject to public health restrictions. If a participant is unavailable, the research team will make multiple contact attempts within the same data collection window. Missed interviews will be documented, and retrospective data will be gathered at the next opportunity.

Follow-up structured research interviews scheduled at 6- and 12 months after randomization, the follow-up interviews will augment the quarterly employment interviews and include measures of health and functionality mirroring those administered at baseline. Additional data collected describes housing, social capital, and health service utilization [21]. Follow-up interviews will be conducted at the same time as the corresponding quarterly employment interviews. As with the quarterly employment interviews, when participants are unavailable for follow-up interview, the research assistant will make several efforts to track and schedule the interview within the designated time until the next quarterly interview period.

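### Annual income and income sources are secondary outcomes to be compared at 6 and 12 months, but the published schedule collects them only at baseline

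*Protocol article*

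**What the plan says.** All references are to the protocol article.

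- **Outcome.** Under Secondary participant-centered outcomes, one of three domains is "Financial well-being: annual income, income sources, and housing stability over the past 12 months". The section says these outcomes are meant to capture change within individuals, and adds: "A detailed schedule of assessments is presented in Table 3".
- **Comparison.** The third objective under Aims and objectives covers employment, financial well-being and health, and states: "Outcomes will be compared between intervention and control groups at baseline, 6 months, and 12 months". The statistical methods section plans mixed models for financial well-being, with effect sizes and 95% confidence intervals.
- **Schedule.** The Outcomes section says: "Table 3 provides a detailed summary of all planned outcomes and associated measures". In Table 3, "income history (annual income, income sources") appears in the row for the baseline participant interview. The follow-up participant interview, timed at "6, 12 months (40–50 min"), lists housing, health service use, BPRS, SF-12, SOFS and RAS-24. The quarterly interview lists weeks, hours, hourly wage and dates for each job.
- **Data-collection text.** The section on plans for assessment says the 6- and 12-month interviews repeat the baseline health and functioning measures. It then says: "Additional data collected describes housing, social capital, and health service utilization". Income is not mentioned there.
- **Timeline.** The sentence introducing Table 5 says: "Participants will be followed for 12 months, with assessments conducted at baseline and quarterly thereafter". As read, the table's time points are -q1, 0, q1 and q2. The last is labelled close-out, and the follow-up participant interview is marked once, under q1.

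**The concern.** A comparison between arms at 6 or 12 months needs a measurement at that time. For annual income and income sources the outcome list and the analysis section assume one, and the schedule does not provide it. If the interview forms are built from Table 3, the trial ends with baseline income only. The planned model and effect size for two of the three financial well-being items then cannot be produced.

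The pilot is intended to supply estimates for planning a later trial, and income is a natural outcome for an employment intervention. Income not asked about during follow-up would have to be recalled later or be lost.

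Table 5 raises a second, smaller question. Its columns do not match the 12-month quarterly schedule that the sentence above it describes.

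**Working it through.** No sample-size, power or error-rate figure bears on this point. The check is a cross-reading of each secondary outcome against Table 3 and the data-collection text, with one quarter taken as 3 months.

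**Step 1. Scheduled post-baseline collection, by outcome**

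| Secondary outcome | Instrument after baseline | Months collected |
|---|---|---|
| Employment status, dates, hours, wages | Quarterly employment interview | 3, 6, 9, 12 |
| Housing | Follow-up participant interview | 6, 12 |
| Health service use | Follow-up participant interview | 6, 12 |
| BPRS, SF-12, SOFS, RAS-24 | Follow-up participant interview | 6, 12 |
| Annual income | none listed | none |
| Income sources | none listed | none |

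Housing is covered for the full year: two look-backs of 6 months give 6 + 6 = 12 months. The gap is therefore 2 of the 3 financial well-being components. It applies to every participant in both arms.

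**Step 2. Can income be rebuilt from the quarterly interview?**

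Earnings per job in a quarter = weeks worked × hours per week × hourly wage. Summed over jobs and over four quarters, this gives 12 months of earnings from reported jobs. It differs from the listed outcome in three ways:

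- It is not total income, because benefits, family support and other non-wage receipts are not asked about.
- It gives no income sources.
- Table 3 frames the quarterly interview around competitive employment, while the comparator section says usual-care placements are generally non-competitive or self-employment. The article does not say whether the per-job items cover such work. If they do not, rebuilt earnings would miss work mainly in the control arm, and the difference between arms would be biased.

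**Step 3. Table 5 against the rest of the article**

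Twelve months of quarterly assessment gives 12 / 3 = 4 quarters: q1 to q4, at months 3, 6, 9 and 12. Interviews at 6 and 12 months fall at q2 and q4.

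| | Table 3 and text | Table 5 as read |
|---|---|---|
| Last quarter | q4 (month 12) | q2 (month 6) |
| Employment interviews | q1, q2, q3, q4 | q1, q2 |
| Follow-up participant interview | q2 and q4 | q1 |

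Two quarters are absent, and neither follow-up interview is in its place.

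**The case against.** **The article condenses a fuller protocol, and the interview forms are not shown.** Table 3's follow-up row is demonstrably incomplete, since the text adds social capital, which that row omits. Income might be missing from it in the same way. This has some force: it means the forms may already contain the items. It does not remove the inconsistency. The article presents Table 3 as covering every planned outcome, and the text that adds social capital does not add income.

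**Job earnings can be computed.** They can, within the limits in Step 2 of the working. Earnings could replace income if the outcome were redefined, but they are not the outcome now listed.

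**The outcome is exploratory.** This stands and limits the severity. The primary outcomes are feasibility measures analysed descriptively. The four progression domains are recruitment, retention, fidelity and acceptability, and none uses income.

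**Table 5 may be damaged.** It was read from a text copy in which table columns can be lost. The treatment rows are also marked only under q1, which would fit a multi-quarter block collapsed into one column. On the other side, four period headings match four time points, and the marks fit four columns. The text cannot settle which it is.

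**A stronger reading.** From Table 5 a reader might infer that no 12-month data will be collected and that none of the 12-month comparisons can be made. The documents do not support that. The outcome section names Table 3 as the schedule. Table 3 and the data-collection text both place an interview at 12 months, and the sentence introducing Table 5 states 12 months of quarterly follow-up.

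**Conclusion.** The point holds for annual income and income sources only. As the article is written, neither has any scheduled value after randomisation, so the planned between-arm follow-up comparison of total income and its sources cannot be made. The 12-month comparisons of employment, housing, service use and health scales remain possible.

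This rests on the follow-up content printed in Table 3 and in the data-collection text. If the unpublished interview forms already ask about income at follow-up, the defect is in the article alone and a correction of the schedule is enough.

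Table 5 is a separate inconsistency to reconcile, subject to a check of the typeset table. It is not evidence that 12-month data will be lost.

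Severity is moderate. The gap should be closed before recruitment, but no primary outcome or progression decision depends on it.

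**What to change.** 1. **Preferred: collect the items.** Add the two baseline income items to the 12-month follow-up interview, in Table 3 and in the data-collection text. At month 12 an annual look-back covers the follow-up year. At month 6 it would reach back 12 - 6 = 6 months before randomisation, so any month-6 item should ask about the past 6 months.
2. **Otherwise: change the outcome.** Either drop annual income and income sources from the secondary outcomes, or redefine the outcome as earnings computed from the quarterly interviews. If redefined, state whether non-competitive work and self-employment count, and apply the same rule in both arms.
3. **Table 5.** Check the typeset table. If it does end at q2, extend it to q4 as close-out, mark the employment interview at q1 to q4, and mark the follow-up participant interview at q2 and q4.

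The first option makes an interview already planned at 40–50 minutes slightly longer and needs a form edit, with no extra visit. The second adds no interview time but gives up total income and its sources as outcomes. The third is an edit to a table. The trial status section says recruitment has not begun, so any of these can be in place for every participant.

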#### Progression criteria for a future definitive trial

Progression to a future definitive trial will be guided by a pre-specified traffic-light framework across four feasibility domains: recruitment, retention, IPS fidelity, and acceptability. Transparent “red–amber–green” thresholds will guide decisions regarding continuation, amendment, or discontinuation of a future trial (Table 4).Recruitment will be assessed as the proportion of achieved versus planned recruitment at matched timepoints during the recruitment period. Recruitment performance will be classified as green if ≥ 85% of the planned recruitment target is achieved, amber if 70–84% is achieved, and red if < 70% is achieved.Retention will be evaluated at the primary follow-up timepoint (12 months). Retention will be classified as green if ≥ 77% of participants are retained, consistent with the retention benchmark anticipated in the study protocol, amber if retention is 60–76%, and red if retention is < 60%.IPS fidelity will be assessed using the IPS-25 Fidelity Scale, a validated instrument widely used to evaluate adherence to the IPS model. Fidelity will be classified as green if the program achieves a score ≥ 100 (indicating good fidelity), amber if scores fall between 74 and 99 (fair fidelity requiring improvement), and red if scores are ≤ 73 (not IPS fidelity).Acceptability will be evaluated using a combination of quantitative participant ratings and qualitative interview data. Quantitative acceptability ratings will be summarized descriptively, and qualitative findings will be interpreted within established implementation science frameworks. Acceptability will be classified as green when quantitative ratings indicate generally favorable perceptions and qualitative data reveal no major barriers to participation; amber when mixed perceptions or remediable barriers are identified; and red when qualitative evidence identifies substantial concerns or barriers that would likely preclude successful implementation of a definitive trial.

**Table 4 Tab4:** Pre-specified progression criteria for feasibility outcomes

Feasibility domain	Green (proceed)	Amber (amend)	Red (stop/reconsider)
Recruitment	≥ 85% of target recruitment achieved	70–84% achieved	< 70% achieved
Retention (12 months)	≥ 77% retained	60–76% retained	< 60% retained
IPS fidelity (IPS-25 scale)	≥ 100 (good fidelity)	74–99 (fair fidelity)	≤ 73 (not IPS fidelity)
Acceptability	Favorable participant ratings and no major implementation barriers	Mixed perceptions or remediable barriers	Major concerns or barriers likely to prevent successful implementation

Progression to a definitive trial will be recommended when no more than one domain is rated red and the overall pattern of findings indicates that identified barriers are remediable and do not threaten the feasibility of the study procedures. In such cases, a remediation plan addressing the red domain will be implemented within a predefined timeframe (≤ 60 days). Amber ratings will trigger predefined amendments to study procedures or implementation strategies. If two or more domains are rated red, the study will be considered not feasible to proceed without substantial redesign.

#### Participant timeline

The schedule of enrollment, intervention delivery, and outcome assessments is summarized in Table 5. Participants will be followed for 12 months, with assessments conducted at baseline and quarterly thereafter.

**Table 5 Tab5:** Participant timeline

Study period	Enrollment	Allocation	Post-allocation	Close-out
Timepoint (quarterly)	-q1	0	q1	q2
Enrollment:				
Eligibility screen	X			
Informed consent	X			
Allocation		X		
Interventions:				
IPS services			X	
Usual services			X	
Assessments:				
Baseline variables	X	X		
Quarterly employment interview			X	X
Follow-up participant interview			X	
IPS Participation Measure (monthly)			X	X
IPS Employment Specialist Log (monthly)			X	X

#### Sample size

The study will include a convenience sample of 120 participants, with 60 allocated to each group. As this is a pilot feasibility trial, no formal power calculation was conducted. Instead, the sample size was determined based on feasibility considerations, alignment with previous IPS pilot studies in similar contexts [17, 18], and the need to generate stable estimates of recruitment, retention, and preliminary variability in outcomes.

This approach is consistent with current methodological guidance for feasibility studies, which emphasizes that sample sizes should be justified according to their ability to assess feasibility parameters rather than to detect statistically significant effects. Feasibility trials aim to inform the design and sample size of a future definitive randomized controlled trial rather than to conduct hypothesis testing or achieve statistical power. The selected sample size is therefore appropriate to evaluate the acceptability, feasibility, and preliminary implementation of the adapted IPS model in this setting and to inform the parameters required for a fully powered RCT [19].

#### Recruitment

The study will implement several recruitment strategies over a 12-month period to enroll 120 participants with 1 year of planned follow-up. Clinicians at the Center for Comprehensive Care in Long-Stay Mental Health will identify potential participants during routine care and refer them to informational sessions offered by the psychosocial rehabilitation service. Promotional materials (e.g., posters and flyers) will be placed in waiting areas and hallways to raise awareness.

Research staff will conduct informational sessions and provide individual outreach to support ongoing recruitment. Individuals who attend a session and express interest in employment will be screened for eligibility, complete the informed consent process, undergo randomization to either usual care or the adapted IPS intervention, and complete the baseline assessment.

Recruitment projections are based on previous IPS trials that achieved consistent enrollment through sustained collaboration with clinical teams and use of incremental recruitment targets [20]. Participant feedback and service utilization data will be used to refine recruitment procedures throughout the study.

### Assignment of interventions: allocation

#### Sequence generation

This study follows a randomized, controlled, outcome-assessor-blinded, parallel-group design. To ensure balance between the intervention (IPS) and control (Usual Care) groups, permuted block randomization with a block size of four will be used. Accounting for an expected 25% attrition rate, the study will recruit 160 participants, arranged in 40 blocks, to meet the target sample size of 120 participants.

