#### Concealment mechanism

A study statistician will generate the randomization sequence in advance using permuted blocks. The sequence will be stored securely in the REDCap system and will not be accessible to study staff, except for the statistician. After the baseline interview, REDCap will assign the intervention based on the pre-generated sequence. A research assistant will facilitate this allocation process during the second recruitment interview.

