#### Procedure for unblinding if needed

As this is an open-label study, no standard procedure for unblinding is required during routine operations. However, if a serious adverse event or exceptional circumstance arises that necessitates revealing a participant’s group assignment, the principal investigator may access the randomization record. Any instance of unblinding, along with its rationale, will be documented and reviewed to ensure adherence to study protocols and ethical standards.

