### Informed consent process

After presenting the IPS pilot study to clinical staff at the Center for Comprehensive Care in Long-Stay Mental Health, clinicians will identify potential participants and refer them to the psychosocial rehabilitation service for an initial informational session. During this session, a trained research assistant will assess eligibility and explain the study’s purpose, procedures, potential risks, and benefits. The assistant will also assess the individual’s capacity to consent using the “Participant Comprehension Assessment Form for Consent.” If the individual lacks capacity to consent, no surrogate consent will be sought. Instead, they will be referred to standard care services.

Individuals who meet all inclusion criteria will be invited to a second informational session, during which the research assistant will review the informed consent form in detail. Participants will be informed that participation is voluntary and that they may withdraw from the study at any time. A copy of the informed consent form will be provided and explained. If the individual agrees to participate, they will sign the form; signed copies will be stored in the research file and provided to the participant. Participants will also be asked for permission to contact a relative. If granted, the relative will receive an explanation of the study’s goals, procedures, risks, and benefits. Other respondents—such as stakeholders at the system, organizational, and provider levels—who are involved in qualitative interviews or focus groups will undergo a tailored consent process, given the potential for disclosure of sensitive or identifiable information.

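### One fixed, published block size of four in an open-label trial lets anyone tracking allocations know a third of them in advance; separately, the Recruitment section puts randomisation before baseline, against two other sections

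*Protocol article*

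**What the plan says.** **Allocation.** Under Sequence generation the article says that "permuted block randomization with a block size of four will be used". On an assumed loss of 25%, it adds that "the study will recruit 160 participants, arranged in 40 blocks, to meet the target sample size of 120 participants". No variation in block size is described. The article is silent on stratification.

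**Concealment.** Under Concealment mechanism, the statistician prepares the list in advance, it is held in REDCap, and no other study staff can open it. REDCap releases the assignment once the baseline interview is done. "A research assistant will facilitate this allocation process during the second recruitment interview." Under Informed consent process, at the first session, "a trained research assistant will assess eligibility"; consent is reviewed at a second session.

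**Blinding.** Under Procedure for unblinding if needed: "As this is an open-label study, no standard procedure for unblinding is required during routine operations." Assignment of interventions: blinding leaves participants, the staff delivering IPS and the research team involved in implementing it unblinded. Outcome interviewers, including those at baseline, are to be blinded.

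**Order of baseline and randomisation.** The Recruitment section has people give consent, then "undergo randomization to either usual care or the adapted IPS intervention, and complete the baseline assessment". Plans for assessment and collection of outcomes says: "Baseline structured interviews will be conducted prior to randomization". Table 5 marks baseline variables under both the enrollment and the allocation columns.

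**The concern.** Hiding the list does not by itself hide the next assignment. With a constant block size that everyone can read in the publication, the remaining contents of a block can be worked out from the assignments already made in it. In an open-label trial those assignments become known to many people. If the next arm is known or strongly suspected, a second session can be brought forward or put off, or a candidate encouraged more or less at consent. The arms could then differ at entry in ways that randomisation was meant to prevent.

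What is at stake is the comparison between arms. Statistical methods for primary and secondary outcomes plans effect sizes with 95% confidence intervals for employment, financial and health outcomes, and Trial design says the pilot should supply estimates for planning a future regional trial.

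The order of baseline and randomisation is a separate matter. If the Recruitment wording were followed, participants would know their arm when giving baseline self-reports such as the SF-12 and RAS-24, and could disclose it to the interviewer who is meant to be blinded.

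**Working it through.** **1. The plan's own figures.** Target 120 with 25% attrition: 120 / (1 − 0.25) = 160. Blocks of four: 160 / 4 = 40. Both figures under Sequence generation reproduce. Sample size speaks of 120 participants (60 per group), so results are given for both totals.

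**2. Certain assignments in a 1:1 block of four.** There are six equally likely balanced sequences. In two of them (AABB, BBAA) the last two assignments are forced; in the other four only the last is forced.

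- Mean forced per block = (2 × 2 + 4 × 1) / 6 = 8/6 = 4/3
- Share = (4/3) / 4 = 33.3%
- 120 × 1/3 = 40; 160 × 1/3 ≈ 53

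**3. Best guess.** Always guess the arm with more places left in the block.

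- First place: 1/2
- Second place: 2/3
- Third place: the first two agree with probability 1/3 (guess certain) and differ with probability 2/3 (guess 1/2), so 1/3 × 1 + 2/3 × 1/2 = 2/3
- Fourth place: 1
- Sum = 1/2 + 2/3 + 2/3 + 1 = 17/6 per block, and (17/6) / 4 = 70.8%
- 120 × 0.708 ≈ 85; 160 × 0.708 ≈ 113; chance would give 60 and 80

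Steps 2 and 3 assume a person who sees every assignment in order and knows where blocks begin.

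**4. Randomly varied sizes.** Simulation with 1,000 runs of 160 assignments, each size equally likely. The guesser knows the set of sizes but not their order and guesses optimally. The sets are illustrative; the article gives none.

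| Block sizes | Certain | Best guess correct |
|---|---|---|
| 4 only | 33.3% | 70.8% |
| 2, 4, 6 | 4.2% | 70.1% |
| 4, 6 | 5.5% | 69.2% |
| 4, 6, 8 | 2.4% | 68.0% |

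The gain is almost all in certain knowledge. With 4, 6 and 8, the advantage over chance falls only from 20.8 to 18.0 percentage points.

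**5. Order of steps, side by side.**

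- Recruitment: consent, randomisation, baseline
- Concealment mechanism: baseline interview, then REDCap assignment
- Plans for assessment and collection of outcomes: baseline, then randomisation
- Table 5: baseline marked in both columns, so it does not settle the order

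Two sections that describe the procedure agree with each other; the Recruitment summary departs from them.

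**The case against.** The list is properly concealed, and nothing in the article says that any individual sees or tracks the run of past assignments. Eligibility assessment and allocation are each given to a research assistant, but not expressly to the same person. This part stands: tracking is an assumption, and the 33% and 71% figures depend on it. What the documents do support is that one role sits at both steps of an open-label trial.

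A reader might infer that, because SMI has no severity cut-off, recruiting staff could bend eligibility. The documents do not support that: Eligibility criteria assigns the diagnosis to the treating psychiatrist in routine care. Eligibility is also assessed at the first session and allocation follows later, so whoever screens knows the relevant slot only if nobody is randomised in between. What remains is the narrower route through timing of the second session and encouragement at consent.

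A single centre is likewise an inference. Eligibility criteria, Recruitment and Informed consent process all name one centre, but Intervention description refers to sites in the plural and the statistical methods mention clustering by site. Several sites sharing one list would make tracking harder.

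On the order of steps, the other side can fairly say that the Recruitment sentence is a summary and that both operational sections put baseline first. A reader might infer that the trial will take baseline data after allocation; the article as a whole points the other way. The finding is an inconsistency to remove. Table 5 may not be perfectly reproduced in the text available, so it carries little weight.

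Finally, the primary outcomes are descriptive, the progression criteria use no between-arm effect, and Sample size disclaims hypothesis testing. That stands and limits the reach of the point.

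**Conclusion.** The point holds in a limited form. A single disclosed block size of four makes one assignment in three certain (about 40 of 120 or 53 of 160) and 71% guessable for someone who learns assignments in order. That someone will do so is an assumption, and single-centre recruitment is the likely reading but is not stated outright. It would be too strong to say that allocations in general are predictable, that concealment is absent, or that staff would manipulate entry. The design leaves an opening that can be narrowed cheaply.

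Any bias would fall on the exploratory between-arm estimates and on what they contribute to planning a definitive trial. The descriptive feasibility outcomes and the progression criteria are not affected.

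The order of randomisation and baseline is a plain conflict between the Recruitment section and two others. Baseline self-reports given with knowledge of the arm, and possible disclosure to the blinded interviewer, would arise only if the Recruitment wording were followed.

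**What to change.** **Block sizes.** Trial status says recruitment has not begun, so the statistician can regenerate the list now with randomly varied sizes, for example 4, 6 and 8. The sizes should be kept in a document not open to recruiting staff, and the article should say only that sizes vary. Certain assignments fall to about 2%; best-guess accuracy stays near 68%, so the change should not be presented as making allocation unguessable. The cost is one new list and, if recruitment stops inside a block of eight, an end imbalance of up to 4 participants. Fixed blocks of four would end level at 120 or 160, as both are multiples of four.

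**Order.** Rewrite the Recruitment sentence as consent, baseline interview, then REDCap allocation, to match Concealment mechanism and Plans for assessment and collection of outcomes. Make Table 5 consistent by showing baseline variables only before allocation. This costs one sentence and one table entry.
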